#### Exclusion criteria

Any participant with severe alcohol dependence defined by the Severity of Alcohol Dependence Questionnaire (SADQ) score ≥ 31.(69) Any participant with mild to moderate dependence will be referred but not excluded.History of IPV severe enough to result in hospitalization in the past 12 months, as MILAP is not designed to address severe levels of violence. Any participant reporting severe IPV cases requiring hospitalization will be referred to tertiary care facilities.Any participant with severe depression, defined by the Patient Health Questionnaire-9 (PHQ-9) score>19 and/or high suicide risk assessed by ninth question of the PHQ-9 (“thoughts that you would be better off dead or thoughts of hurting yourself in some way”) (70) and the Nepal Emergency Suicide Screener-3 (NESS-3) adapted from the Ask Suicide-Screening Questions(71), will be referred to specialized mental health centers for assessment. After discharge from the healthcare facility, they will be approached again for eligibility.Woman who is pregnant; since pregnancy changes the family dynamics and in our study settings, pregnant woman often temporarily moves back to live with their parents where the source of IPV is no longer around. However, if any participant becomes pregnant during the study, she will continue in the study.Cognitive problems/disability precluding participation as self-reported by participant.

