##### Enhanced usual care (EUC):

EUC will be delivered by a separate team of counselors who have completed at least six months of psychosocial training but have not received specialized MILAP training, in order to avoid potential contamination. These counselors will conduct an initial safety assessment and offer: a) WOREC’s IPV rehabilitation services, which include access to a women’s shelter, safety and protection from the perpetrator, mental health counseling, legal support, and health services; b) educational materials on safety planning, the consequences of ongoing IPV, written resources for reducing IPV, and information about a nationwide IPV/DV hotline; c) referrals to wraparound services based on the woman’s needs and priorities, including legal support, safe housing, psychosocial counseling, health services, and livelihood support; d) referral to a one-stop IPV center, along with information about available options, including support for leaving the relationship if the participant expresses that desire.

Since this study includes women currently experiencing IPV, we will enhance the usual care by adding two key services: mental health crisis counseling and a referral pathway for those in need of specialized support.

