**Crisis counseling** will be provided to all participants, regardless of their intervention allocation, who are identified as being at high suicidality risk, as assessed by the study team members using the trigger (ninth) question of the PHQ-9 (“thoughts that you would be better off dead or thoughts of hurting yourself in some way”) and three questions from the NESS-3 that assess imminent suicide risk. Contracted crisis counselors will deliver these services, assess participants’ immediate risk, and provide urgent support as needed. If further care is required, study team members will facilitate referrals to tertiary care facilities. In cases where participants report escalated violence requiring immediate intervention, they will be referred to the One-Stop Crisis Management Center (OCMC) in their respective district. OCMC is a hospital-based center that provides a comprehensive range of services for survivors of gender-based violence, including medical services, psychosocial counseling, legal aid, personal security, rehabilitation and vocational training, coordination with safe homes, and connections to local community-based organizations working in the area of IPV.(76) If a woman doesn’t feel safe or doesn’t wish to return, study team members will connect her with WOREC for access to safe shelter or housing services.

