#### Criteria for discontinuing or modifying allocated interventions {11b}

Participation in this trial will be voluntary and participants can discontinue at any time for any reason. Additionally, we will discontinue participants who are lost to follow-up due to various reasons, including relocation outside the study area or when the family triad no longer resides in the same household. Participants will be considered lost to follow-up if multiple contact attempts fail. These attempts include three consecutive phone calls (Days 1–3), two additional calls on alternate days (Days 5 and 7), attempts to contact to the woman’s listed emergency person (Days 8–10) and a confidential household visit to ensure participant’s well-being. If a missed assessment is found to be due to escalated violence or increased suicidality risk, we will follow established safety protocols and provide crisis management and referrals as needed.

We will not modify intervention allocation during the trial period. However, upon completion of the trial, we will offer and provide MILAP to interested EUC participants.

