#### Participant timeline {13}

After the consent process is completed, we will conduct baseline assessments. This will be followed by the 1:1 random allocation of the recruited participants to either MILAP or EUC. Participants will then receive the intervention based on their allocation. We will conduct follow-up assessments at 1, 3 6, 9, and 12 months from baseline for all participants, regardless of intervention allocation. To evaluate the effectiveness of individual MILAP components, the one-month follow-up assessment will take place immediately after the completion of all MIL-DIL sessions and prior to the start of the BCT sessions. The three-month follow-up will be conducted after participants have completed all nine MILAP sessions. Figure 2 below shows the study timeline.

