#### Plans to promote participant retention and complete follow-up {18b}

We will utilize the strategies we have for intervention adherence (see above) for completing follow-up assessments. We will conduct assessments at a time and place that is convenient and preferred by participants. We will offer breaks as needed during assessments and provide a small financial incentive in appreciation of participants’ time.

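### The discontinuation section ties loss to follow-up both to leaving the shared household and to failed contact, so follow-up of a reachable woman who leaves home is unclear

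*Protocol article*

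**What the plan says.** All references are to the protocol article.

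- **Discontinuation {11b}.** Participants lost to follow-up are to be discontinued. The reasons named include "relocation outside the study area or when the family triad no longer resides in the same household". The following sentence reads: "Participants will be considered lost to follow-up if multiple contact attempts fail". The section then lists phone calls, the emergency contact and a household visit.
- **Enhanced usual care (EUC).** The comparator offers shelter and safe housing, and information on options "including support for leaving the relationship if the participant expresses that desire". In the crisis pathway described in the same section, if a woman feels unsafe or does not wish to return, "study team members will connect her with WOREC for access to safe shelter or housing services". Crisis counseling is for participants in both arms.
- **Participant timeline {13}.** Follow-up assessments run to "12 months from baseline for all participants, regardless of intervention allocation".
- **Retention {18b}.** "We will conduct assessments at a time and place that is convenient and preferred by participants".
- **Exclusion criteria.** Pregnancy at entry excludes because a "pregnant woman often temporarily moves back to live with their parents where the source of IPV is no longer around". For pregnancy after entry: "if any participant becomes pregnant during the study, she will continue in the study".
- **Analysis.** Statistical methods {20a} plan an intention-to-treat analysis at 12 months. Interim analyses {21b} watch for unintended increases in violence or depression. Section {20c} makes multiple imputation conditional on data being missing (completely) at random.

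**The concern.** Not sharing a household is different from being out of contact. A woman in a shelter may answer her phone, and a husband or mother-in-law may move out while the woman stays at her known address. If contact failure is the only test, the household clause has little work to do. If the household clause is a test of its own, the definition that follows does not match it. The clause also resembles the entry requirement that the woman live with her husband and mother-in-law, so field staff could take it for a stopping rule. Two staff members could treat the same woman differently.

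The trial's own care can lead women out of the home, for reasons tied to violence. Support for leaving the relationship is listed only under EUC, so exits may differ by arm. If assessments stopped for these women, the 12-month intention-to-treat comparison would lose them, the safety monitoring would not see their scores, and the missing-at-random condition would be harder to defend, because exposure to violence changes when a woman leaves. A later analysis plan cannot recover assessments that were never made.

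**Working it through.** **Step 1. The rule applied to cases.**

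| Situation | Household or relocation clause | Failed-contact definition |
|---|---|---|
| Woman cannot be traced | may or may not apply | lost |
| Woman in shelter or has left the relationship, reachable | applies | not lost |
| Husband or mother-in-law has moved out, woman reachable | applies | not lost |
| Woman temporarily at her parents' home in pregnancy, reachable | doubtful, since the move is temporary | not lost; exclusion criteria keep her in |

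The two tests disagree in the second and third rows. The section does not say which governs, or whether discontinuing means sessions or assessments.

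**Step 2. The plan's own attrition figure.** Sample size {14} requires 251 and expects about 15% attrition. 251/(1 - 0.15) = 295.3, so 296, which agrees with the 300 planned. 300 × 0.85 = 255 would be analysed. The design falls below 251 once more than 300 - 251 = 49 women (16.3%) are lost for any reason.

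**Step 3. Depression, if leavers are not assessed.** From the documents: EUC 40% with PHQ-9 above 9 (60 of 150) and MILAP 10% (15 of 150), the upper end of the stated 5 to 10%. Assumed: k EUC leavers = 3, 8 or 15; half as many in MILAP; share p of leavers depressed = 20% or 70%. The calculation is complete-case.

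- EUC observed = (60 - pk)/(150 - k)
- MILAP observed = (15 - pk/2)/(150 - k/2)
- Shift = observed difference minus 30 points; a positive value overstates the benefit.

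| p | k | EUC | MILAP | Shift (points) |
|---|---|---|---|---|
| 20% | 3 | 40.4% | 9.9% | +0.5 |
| 20% | 8 | 41.1% | 9.7% | +1.4 |
| 20% | 15 | 42.2% | 9.5% | +2.7 |
| 70% | 3 | 39.4% | 9.4% | 0.0 |
| 70% | 8 | 38.3% | 8.4% | 0.0 |
| 70% | 15 | 36.7% | 6.8% | -0.2 |

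A second set of assumptions fixes stayers at 40% and 10%, varies leavers from 5% of EUC and 2% of MILAP up to 20% and 5%, and sets their depression rate at 10% to 60%. The shift then runs from -1.5 to +6.0 points. The +6.0 needs 20% of EUC women (30 of 150) to leave: all randomised EUC = 0.8 × 40 + 0.2 × 10 = 34%; MILAP = 10%; true difference 24 against 30 in stayers.

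**Step 4. Violence.** The article gives no mean or SD for the violence scale, so only SD units are possible. If leavers differ from stayers by d SD, one arm's mean shifts by dk/150. With d = 1 and k = 15, EUC shifts by 0.10 SD. With half as many MILAP leavers and the same d, the contrast shifts by 1 × (15 - 7.5)/150 = 0.05 SD. The difference detectable with 255 women at 80% power, two-sided 5%, is (1.960 + 0.842) × √(4/255) = 0.351 SD, so 0.05 SD is 14% of it. With d = 0.5 and k = 3 the contrast shifts by 0.005 SD.

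**Step 5. Power.** For 40% against 10%, 80% power needs about 32 women per arm. The depression comparison therefore has ample numbers, and bias is the issue. The 251 comes from the mediation analysis.

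**The case against.** The strongest defence is that the two sentences form one rule with its definition. Only those lost to follow-up are discontinued, relocation and household break-up explain why they were lost, and a reachable woman is not lost. That reading is available. A reader might infer that the protocol plainly orders every woman who leaves home to be dropped; the text does not support this, and the fault is ambiguity.

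A reader might also infer that assessments stop. No sentence says so. The section heading concerns interventions, the timeline schedules assessments for everyone, and the analysis is by intention to treat. The article condenses a longer protocol, which may hold more detail. This makes the harm conditional, but does not settle what discontinuing a participant means in a sentence about loss to follow-up.

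A third inference is that the section contradicts the pregnancy rule and would remove many pregnant women. The exclusion criteria give a specific rule that keeps them, and call the move temporary. No count of pregnancy discontinuations is warranted.

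Three further points stand. Entry requires a wish to stay in the relationship and no stated intention of leaving the area, so leavers should be uncommon. The shelter route is not limited to EUC and no care is prohibited in either arm, so a difference between arms is possible but not shown. The imputation model is not shown and might use residence status. Serious harms would also still be caught by the household visit and the adverse event log.

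**Conclusion.** The section is internally inconsistent on who counts as lost, and leaves open whether a reachable woman who has left home is still assessed. It should be corrected, because on one plausible reading it loses women for reasons tied to a primary outcome and the loss cannot be repaired afterwards.

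The likely size is small and the direction unknown: women who left may have less violence because they are away, or may have left because it escalated. The depression risk difference moves by a few points at most under moderate assumptions, and by 6 at the extreme tested. The violence contrast moves by about 0.05 SD if 15 EUC women leave, MILAP loses half as many and leavers differ by 1 SD. A reader might take the EUC shift of 0.10 SD, 28% of the detectable difference, as the effect on the comparison; that holds only if no MILAP woman leaves. The numbers and outcomes of leavers are all assumed, the figures ignore imputation, and everything depends on assessments actually stopping.

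**What to change.** Amend the discontinuation section {11b} to state that:

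1. Leaving the household or the study area ends only those joint sessions that can no longer be held.
2. Reachable, consenting women stay in all scheduled assessments to month 12 and in the intention-to-treat analysis where this is safe, in person at a place they prefer, as the retention section already allows, or by phone.
3. Lost to follow-up applies only when the listed contact attempts have failed.
4. Temporary moves in pregnancy follow the rule in the exclusion criteria (a cross-reference is enough).
5. Household exits are tabulated by arm and reason for the data and safety monitoring board.

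The cost is a few sentences. Contact details are already collected and updated, and the assessments and staff exist. The downside is extra care for confidentiality when tracing women who have left, and some travel or phone assessments. Recruitment began in April 2025 and is expected to run to March 2027, so the change should be made soon.

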#### Strategies to improve adherence to interventions {11c}

We will employ several strategies to improve participants’ adherence to the intervention. First, we will provide detailed information about MILAP, including its objectives, content, target participants, and the potential benefits of each session, prior to enrollment. Second, we will collect comprehensive contact information from all participants at enrollment (and update it at follow-up assessments), including mobile phone numbers, email addresses (if available), street addresses, nearby landmarks, and the name and phone number of a reliable emergency contact (e.g. a friend or family member). This will help maximize our ability to contact participants for scheduling intervention sessions. Additionally, we will make two reminder calls, one 48 hours and another 24 hours before the scheduled session to minimize the likelihood of missed appointments. Third, we will prioritize participants’ comfort and availability when scheduling sessions and will provide modest compensation for their travel and time.

#### Relevant concomitant care permitted or prohibited during the trial {11d}

We will not prohibit participants from accessing any care during the trial.

#### Provisions for post-trial care {30}

We will offer MILAP to all EUC participants after the completion of trial, if they express interest in receiving the intervention. All participants, regardless of intervention allocation, will receive information on how to access other IPV and mental health services.

#### Outcomes {12}

This study has two primary outcomes. The first primary outcome is the change in the proportion of women with moderate to severe depression from baseline to the 12-month follow-up. To assess depression severity, we will use the PHQ-9, which has been validated in Nepal, and define moderate to severe depression as a PHQ-9 score of greater than nine.(70) The second primary outcome of interest is the change in IPV levels from baseline to the 12-month follow-up. We will assess IPV through measures of abusive control, physical violence, and sexual violence using the Indian Family Violence and Control Scale (IFVCS).(77) Our secondary outcome of interest is the severity of PTSD symptoms, measured by the PTSD CheckList-Civilian Version (PCL-C). Detailed information on primary, secondary and other outcome measures is presented in Table 2.

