MILAP is informed by Social Cognitive Theory (SCT) (54–57) and findings from our pilot studies (Figure 1). SCT offers a culturally appropriate model that emphasizes interpersonal dynamics, the role of family environments in shaping behavior, and strategies to reduce barriers while enhancing facilitators of healthy behavior change.(55, 58) As women in the study setting have fewer options to leave their marriage (19), are heavily affected by the views and behaviors of their family members (37), and are committed to staying married, SCT allows us to incorporate these factors at the women’s individual, interpersonal and family levels. Given that IPV contributes to depression through mechanisms such as social isolation, restricted mobility, diminished self-efficacy and negative family dynamics, MILAP specifically targets determinants identified as modifiable in our prior research.(6–12, 59). Evidence supports the integration of IPV and mental health interventions that build problem-solving skills (60), strengthen relationships with key family members (61, 62), promote social support (63), and enhance resilience and empowerment.(64) MILAP addresses IPV and depression in a non-stigmatizing and depersonalized manner, and offers coping skills for women, mutual empowerment of MILs and daughters-in-law (DILs), and enhanced spousal communication and trust.

We conducted two single-arm pilot studies to test the acceptability, feasibility, and preliminary impact of MILAP, and found it to be well-accepted and effective in addressing IPV, depression and PTSD among young married women.(65, 66) In this manuscript, we report the protocol for a community-based fully-powered two-arm randomized controlled trial involving 300 families to evaluate the effectiveness of MILAP in reducing IPV, and improving depression and PTSD symptoms among **young married women aged 15–24**. Moreover, this randomized controlled trial will include cost-effectiveness analyses to evaluate the health and economic benefits of investing in MILAP, thereby assisting policymakers and payors in assessing MILAP’s potential for future scalability.

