#### Sample size {14}

Given the dual goals of the trial to assess MILAP’s effectiveness and understand mechanisms of action, sample size was determined for both mediation analyses and the impact on primary outcomes. Because mediation analysis is more statistically power-intensive, we calculated the sample size required to achieve 80% power to detect: a) the effect of the intervention on the primary outcome (the proportion of women with at least moderate depression), and b) a significant indirect effect of the intervention on depression, mediated by women’s FOM, one of the primary theorized mechanisms of change in our conceptual model. These calculations were based on the joint testing of both links in the hypothesized mechanistic pathway from intervention to FOM (link 1) and FOM to depression (link 2), using the approach of Vittinghoff and Neilands (78) and the corresponding medssp.R program. Based on our pilot study results, we expect the proportion of women with at least moderate depression (PHQ-9>9) post-intervention to be approximately 40% in the comparison group versus 5–10% in the intervention group. Based on the observed increase in FOM in the pilot study (65, 66), and to ensure clinical relevance, we specified a moderate effect of the intervention on the continuous FOM mediator, i.e., an R^2^ of 13% for FOM, per Cohen’s guidelines(79) for the first link, and an odds ratio of 0.5 per standard deviation (SD) of FOM for the dichotomous depression outcome for the second link of the indirect effect (i.e., a gain of 1 SD in FOM is associated with half the odds of scoring >9 on the PHQ-9). Assumptions for additional nuisance parameters that were necessary to be specified for this sample size calculation were: OR=0.77 for the direct effect of the intervention on depression (i.e., the remaining reduction in odds of PHQ-9 > 9 for the intervention group relative to EUC not mediated by FOM), and ρ_2_ = 0.30, a conventional moderate value (80) to account for correlation between the mediator and potential confounders. Given the 1:1 randomization, intervention exposure is 50% and it is reasonable to assume no confounding (ρ_1_ = 0) of the intervention-depression relationship. Based on these specifications, the required sample size was calculated to be n=251. To account for an anticipated attrition rate of approximately 15%, we determined an initial sample size of n=300 triads.

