### Statistical methods

#### Statistical methods for primary and secondary outcomes {20a}

To evaluate the effectiveness of MILAP in reducing the proportion of women with moderate to severe depression and the levels of IPV and PTSD, we will conduct intention-to-treat (ITT) regression analyses at the end of the trial (12-month follow-up, single timepoint). Additionally, we will perform longitudinal analyses using a two-level regression model, incorporating an interaction between intervention arm and time, with repeated measures nested within participants (i.e., women) and a random intercept for participants. We will use logistic regression models for the binary outcomes (like depression defined by PHQ-9>9), and linear models for the continuous outcomes (like IFVCS score for IPV and PCL-C score for PTSD).

We will use thematic analysis to examine qualitative data from serial in-depth interviews (n = 66 across 22 triads). These interviews will help identify and prioritize potential mediators and moderators for quantitative analysis. We will triangulate the qualitative findings with quantitative data from the full cohort (n = 900 across 300 triads) and conduct a mixed-methods explanatory analysis to develop a comprehensive understanding of the mechanisms through which MILAP produces the intended outcomes and the relative contribution of each mechanism. To explore the mechanisms of change outlined in the conceptual model, we will conduct mediation analyses to assess whether, for example, the DIL-reported freedom of movement (FOM) score mediates the relation between intervention exposure and odds of DIL’s PHQ-9 >9. This will be examined by a structural equation model which simultaneously models the effect of the intervention on FOM (a), and of FOM (b) and intervention (c’) on depression, with a significant indirect effect (a*b) indicating mediation. (85) The model allows for continuous as well as categorical mediators and outcomes, and for multiple mediators to be included in the same model, to compare their relative impact.(86) We will use similar approach for other primary and secondary outcomes.

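### The sample size is said to cover the primary outcomes, but only depression is sized, so adequate power is not shown for the second primary outcome, IPV

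*Protocol article*

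**What the plan says.** Outcomes {12}: "This study has two primary outcomes". The first is the change in the proportion of women with PHQ-9 above nine. For the other: "The second primary outcome of interest is the change in IPV levels from baseline to the 12-month follow-up", measured with the IFVCS.

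Sample size {14} opens with "sample size was determined for both mediation analyses and the impact on primary outcomes". It then narrows: "we calculated the sample size required to achieve 80% power to detect" two things, of which the first is "the effect of the intervention on the primary outcome (the proportion of women with at least moderate depression") and the second is an indirect effect on depression through FOM. The result is n=251, raised to 300 triads for about 15% attrition.

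Background and rationale {6a} calls the study a "community-based fully-powered two-arm randomized controlled trial" that will evaluate effects on IPV, depression and PTSD.

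Statistical methods {20a}: "we will conduct intention-to-treat (ITT) regression analyses at the end of the trial (12-month follow-up, single timepoint"). The next sentence reads "Additionally, we will perform longitudinal analyses using a two-level regression model, incorporating an interaction between intervention arm and time". Depression is modelled by logistic regression and the IFVCS score by a linear model. Neither analysis carries the label primary.

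**The concern.** The Sample size section disagrees with the Outcomes section and with its own opening sentence. One place has two primary outcomes, another sizes one, and the Background claims full power for a list that includes IPV. This is not a detail left to an analysis plan: the article presents a completed sample size calculation and says what it covers.

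The consequence concerns IPV. If the IPV comparison is null at the end, a reader cannot tell whether the trial could have detected a difference worth having, because none was named in advance.

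A second, smaller point follows. With two primary outcomes and two analyses of each, the text should say which analysis decides and whether a claim needs one outcome or both. The lead analysis can be inferred from the wording, but it is not labelled.

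**Working it through.** **Inputs from the article.** 1:1 allocation; 300 triads; about 15% attrition; n=251 required; 80% power; depression 40% versus 5-10%; R² = 0.13 for the intervention on FOM; OR 0.5 per SD of FOM; direct-effect OR 0.77; ρ₂ = 0.30. **Assumed:** two-sided alpha of 0.05, since no alpha or sidedness is stated.

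**1. The plan's own figure.** Without the alpha and the marginal depression prevalence used, 251 cannot be reproduced uniquely. Three routes were tried.
- Direct comparison of proportions: 40% vs 10% needs 32 per arm and 40% vs 5% needs 22 per arm, far below 251 in total.
- Joint test of the two mediation links (normal approximation): total N of 102-123 at prevalence 22.5-25%.
- Total effect implied by the mediation inputs: FOM difference 2 × √0.13 = 0.72 SD; OR = 0.77 × 0.5^0.72 = 0.467; odds 0.667 × 0.467 = 0.311, that is 23.7% against 40%. This needs a total of 250 (logistic Wald) or 256 (two proportions, pooled). It is close to 251, but that this route was used is an inference.

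The attrition step is consistent: 251 / 0.85 = 295.3, rounded up to 300. No route, and no input in {14}, uses an IPV quantity.

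**2. What the sample size offers for IPV.** Evaluable: 300 × 0.85 = 255. For a continuous score with equal arms, the detectable standardised difference is (z for alpha + z for power) × √(4/N):
- alpha 0.05: (1.960 + 0.842) × √(4/255) = 0.351 SD
- alpha 0.025: (2.241 + 0.842) × √(4/255) = 0.386 SD

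Power with 255 evaluable, unadjusted:

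| True IPV difference | alpha 0.05 | alpha 0.025 |
|---|---|---|
| 0.20 SD | 36% | 26% |
| 0.30 SD | 67% | 56% |
| 0.35 SD | 80% | 71% |
| 0.50 SD | 98% | 96% |

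Adjusting for baseline IFVCS helps. With an assumed baseline-to-12-month correlation of 0.5, the detectable difference at 0.05 is 0.351 × √0.75 = 0.30 SD.

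**3. Error rate across two primary outcomes, one analysis each.** If either outcome may support a claim, each at two-sided 0.05: 1 − 0.95² = 9.75% when independent, 9.5% at an outcome correlation of 0.3 and 9.1% at 0.5. If both must succeed, the rate is at most 5%. With 0.025 each it is at most 5% (1 − 0.975² = 4.94% when independent).

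**4. Power cost for depression at 0.025, about 127 per arm.** For 40% vs 5-10%, power stays above 99.9%. For 40% vs 23.7%, it falls from about 80% to about 71%.

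**The case against.** The strongest reply is that much of this is silence rather than error. Alpha, the multiplicity rule and the success rule are commonly left to the analysis plan or full protocol, neither of which is shown. That stands: the article does not show that error control is absent.

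The second reply is that a lead analysis can be read from the text. Both primary outcomes are defined at 12 months, the first analysis named is the 12-month regression, and the longitudinal model is introduced as an addition. This also stands. The remaining point is only that the label is missing.

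The third reply is that IPV may well be adequately powered: 255 women give 98% power for 0.5 SD, and baseline adjustment improves on the unadjusted figures. This is correct, and it limits the conclusion to what is not shown.

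A reader might go further and infer that success on any of four tests (two outcomes by two analyses) would count, with a false-positive rate of roughly 15-18% under assumed correlations. The article does not support that. It writes no either-outcome or any-of-four rule, states no 5% level, and speaks of reducing IPV and depression simultaneously, which is compatible with requiring both. The two-sided rates also count errors in favour of usual care. Errors favouring MILAP are about half: 4.6-4.9% for two tests, against 2.5% for one.

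None of these replies answers the conflict between the Outcomes, Sample size and Background sections over what was sized.

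**Conclusion.** The point holds as an internal inconsistency. The article names two primary outcomes and says the sample size covers them, but sizes only depression and its mediation by FOM. The claim of full power is therefore not shown for IPV. It would be wrong to conclude that the trial is underpowered for IPV: without a target effect, adequacy cannot be judged either way.

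With 255 evaluable and 80% power, the detectable IPV difference is about 0.35 SD at two-sided 0.05, or 0.39 SD at 0.025, unadjusted. These figures rest on an assumed alpha, the stated 15% attrition and a continuous IFVCS score.

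The family-wise rate of about 9-10% is conditional. It applies only if either primary outcome may support a claim at an assumed two-sided 5% each with no control, and not if both must succeed.

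**What to change.** **Sample size {14}.** State that n=251, raised to 300, was derived for depression and its mediation by FOM only. State the alpha. Add the IPV detectable effect (about 0.35 SD at 0.05 or 0.39 SD at 0.025, unadjusted, 255 evaluable, 80% power), with the IFVCS difference considered worth detecting.

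**Background {6a}.** Limit the power claim to what {14} shows.

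**Statistical methods {20a}.** Label the 12-month intention-to-treat regression, adjusted for the baseline value of the outcome, as the primary analysis for each primary outcome, and the arm-by-time model as supportive. Both outcomes are already collected at baseline (Table 2).

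**Success rule.** Say whether one primary outcome or both must succeed. If one is enough, control the family-wise error, for example with Holm (smaller p-value at 0.025, the other at 0.05). A fixed order, or requiring both, would also settle it; if an analysis plan already does so, a reference to it is enough.

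**Cost.** The wording changes are free. Testing at 0.025 costs depression almost nothing at 40% vs 5-10%. At the 40% vs about 24% implied by the mediation inputs, power drops from about 80% to 71%; restoring 80% would need about 312 evaluable, or 312 / 0.85 = about 368 enrolled. Recruitment is expected to run to March 2027, so the clarification can be made before 12-month follow-up is complete.
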